# STUDY TREATMENT

Treatment will not be provided as part of this study.

## Criteria for Permanent Study Discontinuation

6.11 Completion of study.

6.12 The subject or legal guardian refuses further follow-up evaluations.

6.13 The investigator determines that further participation would be detrimental to the subject’s health or well-being.

6.14 The subject fails to comply with the study requirements so as to cause harm to self or seriously interfere with the validity of the study results.

# STATISTICAL CONSIDERATIONS

## General Design Issues

This exploratory study will enroll 82 men and 82 women changing or initiating potent antiretroviral therapy in order to provide cross-sectional and longitudinal analyses of compartmental samples. Blood plasma viral load will be assessed at preentry, entry, week 8 and then every 8 weeks thereafter until week 96, within 30 days of confirmed blood plasma virologic failure, and at the time of premature study discontinuation. Nonblood compartments (saliva and either genital secretions or lymph tissues, or both) will be sampled at study entry (prior to changing or initiating potent antiretroviral treatment); weeks 16, 48, and 96; within 30 days of confirmed blood plasma virologic failure; and at the time of premature study discontinuation. Accrual is anticipated to take approximately 3 years.

Characterization of the viral burden (HIV-1 RNA, proviral DNA) and other characteristics of the virus (genotypic resistance patterns, viral evolution, SI/NSI, fitness, etc.) in compartmental specimens collected at these time points will contribute to understanding of the virologic factors influencing the long-term effect of antiretroviral therapy. Since it is anticipated that the nonblood virologic measures may not be available for all subjects at all time points, the primary

objectives of this study are designed to complement one another and to make optimal use of the available compartmental data.

## Endpoints

7.21 Primary Endpoints

7.211 Virologic failure

For the first primary objective, virologic failure will be defined as confirmed blood plasma HIV-1 RNA > 200 copies/mL at week 16 or later. Subjects without blood plasma HIV-1 RNA at week 16 or later will be considered virologic failures at week 16; subjects without an available confirmatory blood plasma viral load will be considered virologic failures.

7.212 Conditional virologic failure

For the second primary objective, virologic failure will occur at the first of two successive time points (> week 16) where blood plasma HIV-1 RNA is > 200 copies/mL. Subjects without an available confirmatory blood plasma viral load will be considered virologic failures. If a subject does not have virologic failure, the subject will be considered censored at the last time point with a blood plasma HIV-1 RNA measure.

7.213 Virus Detection

The endpoint for the third primary objective is the ability to detect virus from saliva, genital secretions, and lymphoid tissues.

7.22 Secondary Endpoints

7.221 Virologic events

The endpoints for the secondary objectives are the times indicating the loss of virologic suppression in blood and nonblood compartments, and the times of the appearance of HIV-1-drug-resistant mutations not present at baseline in blood and nonblood compartments.

## Sample Size and Accrual

7.31 Virologic Failure

To minimize the assumptions needed to estimate power for the first primary objective, we consider virologic failure as a binary endpoint (yes/no) and model the probability of virologic failure as a function of baseline blood plasma viral load and a nonblood viral load measure. Blood viral load and nonblood viral load are considered to have a bivariate normal distribution with correlation = 0.4 (as observed in ACTG 347 between blood plasma and seminal plasma viral load). The nonblood viral load is dichotomized at its mean, while blood viral load is modeled as a continuous predictor on the log10 scale, with mean = 4.477 log10 copies/mL (30,000 copies/mL) and SD = 0.7 (as observed in ACTG 175).

Power is determined by logistic regression simulations with a two-sided alpha = 0.05, where the effect of the nonblood viral load is evaluated in a model that already contains blood viral load. The rate of virologic failure for a subject with mean levels of the viral load measures is assumed to be 30%. For each log10 higher baseline blood viral load, the odds ratio (OR) for virologic failure is assumed to be 3 (approximately the OR observed in ACTG 364).

With 164 subjects enrolled, it is anticipated that baseline blood and nonblood viral loads will be available for 130 subjects (i.e., a 21% adjustment is made for the possibility of unavailable baseline measures). Then, there is 82% power to detect OR = 3.5, comparing subjects with high nonblood viral loads versus low nonblood viral loads in terms of virologic failure. This corresponds to a probability of virologic failure of 44% for a subject with high nonblood viral load compared with a probability of 19% for a subject with low nonblood viral load, both subjects having similar blood viral loads.

Similarly, there is 72% power to detect an OR = 3; this corresponds to virologic failure probabilities of 43% versus 20% for subjects having high and low nonblood viral loads, respectively.

Note that these power statements can be considered conservative, in that higher power is expected if the nonblood viral load is modeled as a continuous variable or if time-to-event methods are used instead of the binary, logistic regression approach used for the power calculations (and more so if the virologic failure rate is higher).

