4.32 Compartmental Evaluations

4.321 Whole blood willbe collected for storage of plasma and PBMC samples (see Appendix II). The following evaluations will be performed unless totalblood volumes exceed safe limits (the American Red Cross has a limit of 450 mL of blood over 56 days for healthy volunteers):

 Plasma for HIV-1 genotypic resistance studies.

 PBMC storage for HIV-1 proviral DNA studies.

NOTE: If the subject is enrolled in other studies and blood volumes do not permit obtaining an additional blood sample for A5077, the A5077 protocol team will request access to plasma and PBMC samples from the coenrolled study(ies) (see Appendix II).

4.322 Saliva: Samples of saliva should be obtained, processed, stored, and shippedas outlined in Appendix III. The following evaluations will be performed:

 HIV-1 RNA quantitation.

 HIV-1 genotypic resistance studies.

 HIV-1 proviral DNA studies.

4.323 Genital Secretions and/or Lymphoid Tissues: Subjects have the option to contribute either genital secretions or lymphoid tissues, or both. Samples should be obtained, processed, stored, and shipped as outlined in Appendices IV and V. The following evaluations will be performed:

 HIV-1 RNA quantitation.

 HIV-1 genotypic resistance studies.

 HIV-1 proviral DNA studies.

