7.32 Conditional Virologic Failure

It is assumed that 61% of the enrolled subjects will be on study, have a week 16 nonblood viral load measurement, have blood plasma HIV-1 RNA < 200 copies/mL at week 16, and haveat least one subsequent blood plasma viral load measure, implying a sample size of 100 for the analysis of the second primary objective. The proportion of these subjects with detectable nonblood viral load is expected to depend on the compartment of interest and also on the assay method.

Kovacs et al. (45)reported that 26% of women with blood plasma HIV-1 RNA < 500 copies/mL had detectable HIV-1 in the genital tract. It was observed in ACTG 320/866 that out of 11 (9 at week 24 and 2 at week 40) paired on-treatment blood plasma and female genital tract specimens in which blood plasma HIV-1 RNA was undetectable (< 400 copies/mL by NucliSens), 9% (one) had detectable HIV-1 RNA in the genital tract (> 400 copies/mL by NucliSens). It was observed in ACTG 347/850 that 6% (one) of 17 men with undetectable blood plasma HIV-1 RNA (< 400 copies/mL by NucliSens) at week 16 had detectable seminal plasma viral load (HIV-1 RNA > 400 copies/mL by NucliSens). Dornadula et al. (5)reported that 45% (10) of 22 subjects (20 men and 2 women) with blood plasma HIV-1 RNA < 50 copies/mL had detectable viral HIV-1RNA levels in genital fluids. Hence, power statements for the second primary objective are given for a variety of scenarios. As above, virologic failure is considered as a binary endpoint.

If 40% of these 100 subjects have detectable nonblood viral load, then there is 80% power to compare subsequent blood plasma virologic failure rates of 5% versus 26% (similarly 80% power for 10% versus 34% and for 15% versus 42%), comparing subjects with low versus high levels of a nonblood viral load measure at the time of suppressed blood viral load. If 20% of these 100 subjects have detectable nonblood viral load, then there is 80% power to compare subsequent blood plasma virologic failure rates of 5% versus 33% (similarly 80% power for 10% versus 41% and for 15% versus 49%).

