7.33 Virus Detection

Prior data suggest that the probability of detecting virus from genital secretions differs between men and women with suppressed blood plasma HIV-1 RNA levels (with higher rates observed in women), so men and women will be assessed separately. It is assumed that 25 men and 25 women will remain on study through week 48, have a week 48 genital secretion specimen available, and have persistently suppressed blood plasma viral loads (< 200 copies/mL) from week 16 through week 48.

The following table describes 95% confidence intervals (in particular, showing their width) for various possible realizations of the data for the genital secretions aspect of the third primary objective.

Table 1. Confidence Intervals for a Percentage

| Observed | Percentage | Exact  95% CI |
| --- | --- | --- |
| 1/25 | 4% | 0 - 20% |
| 2/25 | 8% | 1 – 26% |
| 3/25 | 12% | 3 - 31% |
| 4/25 | 16% | 5 – 36% |
| 5/25 | 20% | 7 – 41% |
| 6/25 | 24% | 9 – 45% |
| 8/25 | 32% | 15 – 53% |
| 10/25 | 40% | 21 – 61% |
| 12/25 | 48% | 28 – 69% |
| 15/25 | 60% | 39 - 79% |

The above table may also be appropriate for assessing confidence interval width for detecting virus in lymph tissues among subjects with persistently suppressed blood plasma HIV-1 RNA levels (grouping men and women together, using the same assumptions as above and assuming that lymph tissue at week 48 will be available with one-half the probability of genital secretion specimens, thus yielding a total of 25 subjects).

Table 2 describes 95% confidence intervals for the saliva aspect of the third primary objective (grouping men and women together and using the same assumptions as for genital secretions, thus yielding a total of 50 subjects).

Table 2. Confidence Intervals for a Percentage

| Observed | Percentage | Exact  95% CI |
| --- | --- | --- |
| 2/50 | 4% | 0 – 14% |
| 4/50 | 8% | 2 – 19% |
| 6/50 | 12% | 5 – 24% |
| 8/50 | 16% | 7 – 29% |
| 10/50 | 20% | 10 – 34% |
| 12/50 | 24% | 13 – 38% |
| 16/50 | 32% | 20 – 47% |
| 20/50 | 40% | 26 – 55% |
| 24/50 | 48% | 34 – 63% |
| 30/50 | 60% | 45 - 74% |

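### The 82%/72% and 80% power figures for primary objectives 1 and 2 are not limited by compartment, but on the halving used in section 7.33 lymphoid tissue would have only about 40–60% power

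*Protocol*

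**What the plan says.** Section 7.31 (objective 1) models the probability of virologic failure "as a function of baseline blood plasma viral load and a nonblood viral load measure". It gives one analysable number: "With 164 subjects enrolled, it is anticipated that baseline blood and nonblood viral loads will be available for 130 subjects". The step from 164 to 130 is a single allowance: "a 21% adjustment is made for the possibility of unavailable baseline measures". At 130 the section states 82% power for an odds ratio of 3.5 and 72% for an odds ratio of 3.

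Section 7.32 (objective 2) takes 61% of those enrolled, "implying a sample size of 100 for the analysis of the second primary objective". It recognises that the proportion with detectable virus will differ by compartment and assay, and gives 80% power scenarios at 40%, 20% and 10% detectable. The total of 100 is the same in all of them.

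Sampling is not the same for every compartment. The Schedule of Events requires saliva of all subjects. For the rest, section 4.32 says: "Subjects have the option to contribute either genital secretions or lymphoid tissues, or both".

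Section 7.33 (objective 3) does size by compartment. It assumes 25 men and 25 women with genital specimens and puts saliva at 50 on the same assumptions. For lymph tissue it arrives at 25 by "assuming that lymph tissue at week 48 will be available with one-half the probability of genital secretion specimens".

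**The concern.** Objectives 1 and 2 (sections 2.11 and 2.12) concern nonblood compartments in general, so a reader of 7.31 and 7.32 will take 82%/72% and 80% as describing each compartment, lymphoid tissue included. The protocol's only statement about how often lymphoid tissue will be available relative to another compartment is the one-half ratio in 7.33. That ratio is used for objective 3 and not carried into objectives 1 and 2. Sections 7.31 and 7.32 also call their power statements conservative, citing continuous modelling and time-to-event methods, without mentioning that the number of subjects may be smaller in some compartments.

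At stake is how the lymphoid results of two primary objectives are read. If the analysis has roughly even odds of detecting the planned effect, a null finding there says little, and the stated power would suggest otherwise.

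**Working it through.** **Inputs from section 7.31.** "Power is determined by logistic regression simulations with a two-sided alpha = 0.05"; failure 30% at mean levels; odds ratio 3 per log10 of blood viral load, SD 0.7; blood–nonblood correlation 0.4 (from seminal plasma data); nonblood load split at its mean; 164 enrolled, 21% allowance.

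**Inputs from section 7.32.** 61% of 164; two-tailed Fisher exact test at 0.05; nine pairs of failure rates, from 5% versus 26% (40% detectable) to 15% versus 62% (10% detectable).

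**Step 1: the plan's numbers of subjects.** 164 × (1 − 0.21) = 129.6, or 130. 164 × 0.61 = 100.0. Both agree with the plan.

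**Step 2: the plan's power for objective 1.** Model: logit P(failure) = a + ln(3) × (blood load − mean) + ln(OR) × H, where H = 1 for high nonblood load and a = logit(0.30) − ½ ln(OR), so that 30% lies midway between high and low. The implied failure probabilities are 44.5% and 18.6% for odds ratio 3.5 (plan 44% and 19%), and 42.6% and 19.8% for odds ratio 3 (plan 43% and 20%). Simulated power of the two-sided Wald test at n = 130 is 83–84% for odds ratio 3.5 and 73–74% for odds ratio 3. The plan's 82% and 72% are reproduced within about 2 points.

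**Step 3: the plan's power for objective 2.** Full enumeration of the Fisher test at N = 100 gives, over the nine scenarios:
- 79.5–81.5% when each tail is tested at alpha/2. This matches the plan's 80% and is probably the convention used.
- 81–89% with the ordinary two-sided Fisher p-value, so the stated 80% is met or exceeded.

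**Step 4: numbers for lymphoid tissue.** Take 130 and 100 as the numbers for the best-sampled compartment, and carry the 7.33 ratio of one-half to baseline and week 16 (an assumption; 7.33 states it for week 48 only). Lymphoid n = 130 × ½ = 65 for objective 1 and 100 × ½ = 50 for objective 2.

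**Step 5: power at those numbers, same models and effects.**

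| Analysis | Stated | Lymphoid n | Power at that n |
|---|---|---|---|
| Objective 1, OR 3.5 | 82% | 65 | about 52–53% |
| Objective 1, OR 3 | 72% | 65 | about 43–44% |
| Objective 2, alpha/2 per tail | 80% | 50 | about 40–50% |
| Objective 2, ordinary two-sided Fisher | 80% | 50 | about 49–62% |

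The one-point spread for objective 1 is simulation error between runs. The ranges for objective 2 are over the nine stated pairs of rates.

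**Step 6: genital secretions.** Section 7.33 gives them the same availability as saliva (25 + 25 = 50). With that parity, genital n can reach 130 and 100. The protocol states no uptake rate for baseline or week 16. The lowest value compatible with the one-half ratio, if every analysed subject gives at least one of the two samples, follows from g + g/2 ≥ 1, so g ≥ 2/3: 130 × 2/3 ≈ 87 and 100 × 2/3 ≈ 67. This floor requires that nobody gives both samples, and it departs from the parity in 7.33.

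**The case against.** The strongest reply is that nothing has been miscalculated. The stated powers reproduce, and neither section says that lymphoid tissue will supply 130 or 100 subjects. The inputs are largely genital: the correlation comes from seminal plasma, and all the detectability data cited in 7.32 are from genital samples. Section 7.1 calls the study exploratory and expects nonblood measures to be missing for some subjects, and 7.4 plans periodic checks of sample availability. The one-half ratio is stated only for week 48.

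Most of this stands, and it bounds the point. The fault is one of scope, not arithmetic, and the ratio at baseline and week 16 has to be declared as an assumption. But these are primary objectives with explicit power claims for an unnamed nonblood measure. The only allowance for missing samples is one blanket percentage per objective, while 7.33 shows that compartment-specific numbers were considered for the third objective.

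A reader might go further and infer that only saliva can reach 130 and 100, because genital secretions are optional too. The documents do not support that. A subject may give both optional samples, so one does not displace the other, and 7.33 sizes saliva on the same assumptions as genital secretions. A genital shortfall towards 87 and 67 is possible if many subjects give lymphoid tissue alone, but nothing in the protocol implies it. The same applies to lymphoid numbers below 65 and 50.

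**Conclusion.** The point holds for lymphoid tissue. Sections 7.31 and 7.32 attach 82%/72% and 80% power to any nonblood measure. On the availability ratio in 7.33, lymphoid tissue would have about 65 and 50 subjects, with power of about 52–53% and 43–44% for objective 1 and about 40–62% for objective 2, depending on the Fisher convention and scenario.

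This rests on two assumptions: that the week-48 ratio also applies at baseline and week 16, and that 130 and 100 describe the best-sampled compartment. A higher lymphoid uptake would narrow the gap and a lower one would widen it. For saliva the stated figures stand. For genital secretions they stand if nearly all subjects choose to give them, as the parity in 7.33 supposes. Restricting the figures to saliva alone would conflict with that parity.

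**What to change.** In 7.31 and 7.32, state that the 130 and 100 subjects, and the 82%/72% and 80% power, apply to saliva and, provided uptake matches the parity assumed in 7.33, to genital secretions. Add one line in each section for lymphoid tissue giving the expected number (about 65 and 50 if the one-half ratio is adopted for baseline and week 16) with either the resulting power or the odds ratio and failure rates detectable with 80% power. If the sponsor expects a different lymphoid uptake at those visits, it should state that rate and use it. In 7.32, also say which two-tailed Fisher convention was used, since this shifts the lymphoid figures by several points.

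The cost is wording and less favourable stated figures for lymphoid tissue. No patients, visits or procedures are added.

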7.32 Conditional Virologic Failure

It is assumed that 61% of the enrolled subjects will be on study, have a week 16 nonblood viral load measurement, have blood plasma HIV-1 RNA < 200 copies/mL at week 16, and haveat least one subsequent blood plasma viral load measure, implying a sample size of 100 for the analysis of the second primary objective. The proportion of these subjects with detectable nonblood viral load is expected to depend on the compartment of interest and also on the assay method.

Kovacs et al. (45)reported that 26% of women with blood plasma HIV-1 RNA < 500 copies/mL had detectable HIV-1 in the genital tract. It was observed in ACTG 320/866 that out of 11 (9 at week 24 and 2 at week 40) paired on-treatment blood plasma and female genital tract specimens in which blood plasma HIV-1 RNA was undetectable (< 400 copies/mL by NucliSens), 9% (one) had detectable HIV-1 RNA in the genital tract (> 400 copies/mL by NucliSens). It was observed in ACTG 347/850 that 6% (one) of 17 men with undetectable blood plasma HIV-1 RNA (< 400 copies/mL by NucliSens) at week 16 had detectable seminal plasma viral load (HIV-1 RNA > 400 copies/mL by NucliSens). Dornadula et al. (5)reported that 45% (10) of 22 subjects (20 men and 2 women) with blood plasma HIV-1 RNA < 50 copies/mL had detectable viral HIV-1RNA levels in genital fluids. Hence, power statements for the second primary objective are given for a variety of scenarios. As above, virologic failure is considered as a binary endpoint.

If 40% of these 100 subjects have detectable nonblood viral load, then there is 80% power to compare subsequent blood plasma virologic failure rates of 5% versus 26% (similarly 80% power for 10% versus 34% and for 15% versus 42%), comparing subjects with low versus high levels of a nonblood viral load measure at the time of suppressed blood viral load. If 20% of these 100 subjects have detectable nonblood viral load, then there is 80% power to compare subsequent blood plasma virologic failure rates of 5% versus 33% (similarly 80% power for 10% versus 41% and for 15% versus 49%).

If 10% of these 100 subjects have detectable nonblood viral load, then there is 80% power to compare subsequent blood plasma virologic failure rates of 5% versus 44% (similarly 80% power for 10% versus 53% and for 15% versus 62%). This is based on a two-tailed Fisher exact test, alpha = 0.05. Note that these power statements can be considered conservative, in that higher power is expected if the nonblood viral load can be modeled as a continuous variable (when it is detectable), or if time-to-event methods are used instead of the comparison of proportions (and more so if the virologic failure rate is higher).

7.33 Virus Detection

Prior data suggest that the probability of detecting virus from genital secretions differs between men and women with suppressed blood plasma HIV-1 RNA levels (with higher rates observed in women), so men and women will be assessed separately. It is assumed that 25 men and 25 women will remain on study through week 48, have a week 48 genital secretion specimen available, and have persistently suppressed blood plasma viral loads (< 200 copies/mL) from week 16 through week 48.

The following table describes 95% confidence intervals (in particular, showing their width) for various possible realizations of the data for the genital secretions aspect of the third primary objective.

Table 1. Confidence Intervals for a Percentage

| Observed | Percentage | Exact  95% CI |
| --- | --- | --- |
| 1/25 | 4% | 0 - 20% |
| 2/25 | 8% | 1 – 26% |
| 3/25 | 12% | 3 - 31% |
| 4/25 | 16% | 5 – 36% |
| 5/25 | 20% | 7 – 41% |
| 6/25 | 24% | 9 – 45% |
| 8/25 | 32% | 15 – 53% |
| 10/25 | 40% | 21 – 61% |
| 12/25 | 48% | 28 – 69% |
| 15/25 | 60% | 39 - 79% |

The above table may also be appropriate for assessing confidence interval width for detecting virus in lymph tissues among subjects with persistently suppressed blood plasma HIV-1 RNA levels (grouping men and women together, using the same assumptions as above and assuming that lymph tissue at week 48 will be available with one-half the probability of genital secretion specimens, thus yielding a total of 25 subjects).

Table 2 describes 95% confidence intervals for the saliva aspect of the third primary objective (grouping men and women together and using the same assumptions as for genital secretions, thus yielding a total of 50 subjects).

Table 2. Confidence Intervals for a Percentage

| Observed | Percentage | Exact  95% CI |
| --- | --- | --- |
| 2/50 | 4% | 0 – 14% |
| 4/50 | 8% | 2 – 19% |
| 6/50 | 12% | 5 – 24% |
| 8/50 | 16% | 7 – 29% |
| 10/50 | 20% | 10 – 34% |
| 12/50 | 24% | 13 – 38% |
| 16/50 | 32% | 20 – 47% |
| 20/50 | 40% | 26 – 55% |
| 24/50 | 48% | 34 – 63% |
| 30/50 | 60% | 45 - 74% |

